## Abstract

**Background:**

Cerebral palsy (CP) is the most common motor disability in childhood (2 to 3 per 1000 live births), and is frequently accompanied by cognitive impairments and behavioural problems. Children with CP are at increased risk of attention deficit disorder with or without hyperactivity (Attention Deficit Disorder (ADD)/Attention Deficit Hyperactivity Disorder (ADHD)) including working memory deficits. The primary aim of this study is to evaluate if cognitive training may improve working memory in children with CP.

**Methods/Designs:**

The study is an investigator-blinded, randomized controlled trial with a stepped-wedge design that will include 115 schoolchildren with CP. Eligible for participation are children with CP, aged 7 to 15 years, who are able to follow instructions and handle a computer mouse. Exclusion criteria are the presence of photosensitive epilepsy, Gross Motor Function Classification System (GMFCS) level V (most severe CP) (Phys Ther 80: 974-985, 2000) and severe visual or hearing impairments. Following assessment of eligibility and baseline cognitive assessment the participants will be randomized to either cognitive working memory training or treatment-as-usual (‘control group’). The intervention is a computer-based working memory training program consisting of 25 daily sessions to be performed over a 5 to 6-week period at home. A neuropsychological assessment will be performed before and 4 to 6 weeks after completed training. When the latter assessment has been completed in the intervention group, the ‘control group’ will start on the same training program. Both groups will meet for a final neuropsychological assessment six months after completed training by an examiner unaware of group adherence.

**Discussion:**

There is limited evidence for the effect of most interventions in children with CP, and evidence is completely lacking for interventions aiming to improve deficits in cognition, learning and behaviour. The proposed multicenter study, will bring forth comprehensive information about cognitive, neuropsychological, and daily-life functioning in children with CP aged between 7 and 15 years. In addition, the study will be the first to evaluate the effects of an intervention method to improve working memory in children with CP. If successful, computer-based working memory training may represent an efficient and cost-effective intervention for this group of children.

**Trial registration:**

ClinicalTrials.gov Identifier: NCT02119364

## Background

Cerebral palsy (CP) is the most common motor disability in childhood (2 to 3 per 1000 live births), and is frequently accompanied by cognitive impairments and behavioural problems
[1-4]. Treatment and rehabilitation of patients with CP requires a broad-based and longterm interdisciplinary approach. Children with CP are at increased risk of attention deficit disorder with or without hyperactivity (attention deficit disorder (ADD) and/or attention deficit hyperactivity disorder (ADHD))
[4] and working memory deficits
[5]. CP with cognitive deficits represents significant burdens on patients, their families and the society. Even so, evidence-based treatment is lacking for most treatment modalities for children with CP in general, and completely for interventions aiming to improve deficits in cognition, learning and behaviour
[6].

The present study is a multicenter controlled clinical trial involving children and researchers from three of five different health regions in Norway, as well as the Norwegian University of Science and Technology (NTNU), and its main research goal will be to evaluate the effects of computer-based cognitive training in children with CP. In addition, this study will be the first to include a comprehensive neuropsychological examination to improve our understanding of cognitive impairments and deficits, as well as cognitive capabilities in children with CP to aid in intervention planning and rehabilitation services.

Cerebral palsy is caused by injuries or developmental anomalies that may involve the cerebral cortex and white matter, deep grey matter nuclei and cerebellum of the developing, immature brain. The brain injury is primarily associated with motor impairments, but also with deficits affecting perception, speech, communication and cognition including deficits in attention and reduced executive functions
[3,7-9]. However, children with CP constitute a heterogeneous group and the clinical picture depends on the timing, extent and localization of the brain injury. The two most common subtypes are spastic unilateral and spastic bilateral CP. The unilateral subtype is most common among children born at term, where one main cause is thought to be a vascular catastrophe of the main cerebral arteries (perinatal ‘stroke’)
[10]. Approximately half of the stroke cases have their brain damage on the right side, the other half on the left side
[8]. Children with unilateral CP have less severe motor impairments and less cognitive problems than those with bilateral CP
[11]. Nonetheless, the unilateral group has a significantly increased risk of attention problems, even as pre-school children, as assessed by their parents and teachers as compared to healthy children
[4]. Cognitive impairments and problems with attention and executive functions are more common among children with CP than among typically developing children
[12-16]. Among preterm born children, both with and without CP, cognitive impairments including reduced working memory and high prevalence of ADHD persist into adulthood
[17-19].

Working memory represents a central component of attention and executive functions and may be defined as the ability to keep information ‘online’ and at the same time manipulate the information. Working memory is regarded a contemporary storage system that is under attention control
[20] and supports our ability for goal-directed behavior and other higher order cognitive processes required in situations that are novel
[20]. It is also considered to be a prerequisite for other executive functions, such as reasoning and planning, and for predicting intelligence and academic success
[21,22]. Functional brain imaging has shown that working memory is primarily supported by a neuronal network in the frontal and parietal lobes
[23] and that increased activity in these areas of the brain correlates positively with measures of working memory capacity
[24]. Executive and attention functions describe the ability to self-regulate behaviour, cognition and emotions
[25,26]. These functions are primarily localized in the frontal part of the brain. Since the frontal lobe of the brain is connected to other brain areas through fronto-parietal tracts as well as long association tracts, brain injuries in parts of the brain other than the frontal lobe that affect connectivity may also lead to symptoms of frontal lobe impairment
[27]. Both we
[4,18,28,29] and other authors
[30-32] have reported that children born preterm and children with CP have an increased prevalence of symptoms of reduced attention and problems with working memory similar to the problems found in children with ADD and/or ADHD.

There is also a lack of studies examining how cognitive deficits may differ between children with various CP subtypes and within the same subtype; for example in children with the spastic unilateral CP subtype, between those with an injury on the right and left side of the brain, respectively. In adults suffering from stroke it is unclear whether a right or left side brain injury affects working memory differently
[33]. In a recent study by Laures-Gore *et al*.
[33] stroke patients with a left brain injury had more impaired verbal working memory than those with an injury on the right side, consistent with an early report by Black and Strub
[34]. However, other studies have not found any differences in working memory between right and left side brain damage after stroke in adults
[35]. In children with CP this has, to the best of our knowledge, not been studied despite the higher prevalence of attention problems. The extent of more specific problems, such as with working memory, may depend on CP subtype and be related to perinatal complications
[36]. The spastic bilateral subtype that mainly involves the lower extremities (known as diplegic CP) is particularly common in children born preterm
[10]. In preterm children, tracts and networks of neural connections in the brain are particularly susceptible to damage due to reduced perfusion and oxygen supply to the periventricular water-shed areas in deep white matter
[37]. Injuries in these areas, where projectional cortico-spinal motor tracts, especially to the lower extremities, are passing through and may be damaged, explain the motor impairment. However, such diffuse or focal white matter injuries may also lead to problems of perception, cognition, attention and other higher brain functions (executive function) caused by damage to commissural and association tracts with compromised connectivity and networking
[7]. Few studies have assessed attention and executive functions in preterm born children with CP but one study reports that children with spastic diplegic CP do have problems with inhibition control likely caused by deep white matter damage
[14]. Learning difficulties and problems with social functioning have also been described in children with spastic diplegic or hemiplegic (affecting one side of he body) CP due to impaired attention and executive functions
[25]. In young adults born very preterm with a birth weight of less than 1500 grams, a study by Løhaugen *et al.* indicated that working memory may be especially impaired in those with CP, even into adulthood
[18].

### Training of working memory

Until recently it was believed that working memory could not be influenced by stimulation or training. However more recent research, including our own at NTNU, has shown that working memory capacity can be improved through cognitive training
[16,38-40]. A computer-based program (Cogmed Robomemo™, http://www.pearsonassessment.com) for the training of working memory of children with ADHD was developed by [name] at the Karolinska Institute in Stockholm in 1999, and the first training results were published in 2002
[38]. The program improved working memory in the trained tasks; however, tasks not trained in the program also improved. This indicated a generalization effect to tasks such as understanding room-direction and complex problem solving
[38]. The findings were confirmed in a randomized controlled trial of children with ADHD showing that Cogmed Robomemo™ training improved both verbal and visual working memory and that the parents reported fewer symptoms of inattention in their children after completion of the training
[41]. These studies were, however, limited to participants without general learning difficulties or cognitive impairments. In the first Robomemo study that included adolescents born with an extremely low birth weight (birth weight of less than 1000 grams), Løhaugen *et al.*[42], included participants with intellectual impairments and two participants with CP (17). They found that even when these participants were included the Cogmed Robomemo™ intervention improved working memory. The positive effect was observed on trained as well as untrained tasks, and also on memory and reduced symptoms of ADHD
[16]. Other studies have shown that children without ADHD but with difficulties with working memory, can improve their working memory with training
[43]. These findings suggest that training of working memory may have significant impact on academic performance.

### How does training affect the brain and what are the possible biological mechanisms?

Studies have shown that training of working memory also induces neurobiological changes such as increased activity in the prefrontal cortex and the parietal lobe
[44]. These areas are associated with response inhibition and the ability to reason
[24]. Overlapping neural systems could be a reasonable explanation of the generalized effects of working memory training to other cognitive functions. Furthermore, training of working memory has been shown to increase the density of dopamine receptors in the prefrontal cortex
[45] and has also been associated with structural changes in the white matter of the brain
[46]. This is in support of a training-induced plasticity of the neural networks underlying working memory, response inhibition and the ability to reason. If working memory and executive functioning can be improved by training it would be reasonable to assume that training will also have an effect on the activities in daily life that are dependant on working memory. A third mechanism constitutes changes in white matter microstructure. Working memory capacity is associated with the integrity of the white matter network between the parietal and the frontal lobes
[47]. Takeuchi *et al.* found higher fractional anisotropy (FA) values in parietal white matter tracts parallel to corpus callosum after working memory training in healthy elderly adults, indicating improved microstructure
[46]. The degree of increase in FA depended on the magnitude of training. This may be explained by improved myelination leading to an increased efficiency of signal transfer between the different parts of the brain. Increased cortical thickness in healthy controls after memory training has also been reported
[48].

## Methods/Design

### Objectives

The main goals of the present study are as follows: To present cognitive profiles reflecting neuropsychological functions in children with different subtypes of CP with varied aetiology. Also, to study of a computer-based training program can improve the working memory capacity of children with CP (near transfer effect), and improve learning abilities and behaviour. While learning abilities are assessed by neuropsychological learning and memory tests, behaviour will be assessed by questionnaires (the Vineland Adaptive Behaviour Scale and ADHD rating scale) given to parents and school teachers (far transfer effect). If the intervention is effective, will the beneficial effects persist over time? Assessment will include questionnaires and neuropsychological tests at six months post-training.

To present cognitive profiles reflecting neuropsychological functions in children with different subtypes of CP with varied aetiology.

To study if a computer-based training program can:

Improve the working memory capacity of children with CP (near transfer effect).

Improve learning abilities and behaviour. While learning abilities are assessed by neuropsychological learning and memory tests, behaviour will be assessed by questionnaires (the Vineland Adaptive Behaviour Scale and ADHD rating scale) given to parents and school teachers (far transfer effect).

If the intervention is effective, will the beneficial effects persist over time? Assessment will include questionnaires and neuropsychological tests at six months post-training.

This study will provide new knowledge on the effectiveness of a computer-based cognitive training program in improving the daily-life function and behavioral problems of children with CP. We hypothesize that neuropsychological deficits and impairment will be frequent in this group. Our main hypotheses are that working memory can be improved through cognitive training in children with bilateral as well as unilateral CP, the two most common CP subtypes. We also hypothesize that improved working memory will result in improved learning abilities and less symptoms of inattention.

### Design

The study is a multicentre, clinical controlled trial applying a stepped-wedge design, as described by Brown and Lilford
[49]. The children will be examined at baseline (before the start of training - t1) and immediately after completed training (after four to six weeks - t2). According to the stepped-wedge design, group 1 will start training while the other group will wait and serve as the control. Group 2 will then start training when group 1 has completed its training (Figure 
1). This design ensures a well matched control group enabling adjustment for the natural cognitive development that occurs over time. Group 1, the first to receive the training, will also meet for the follow up after group 2 has finished the training to ensure that the researchers remain blinded to group adherence throughout the study (t3). All participants will meet for a longterm follow-up six months after completing training for each group respectively (t4). The primary endpoint will be the assessment performed at four to six weeks after training (t2 and t3).

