### Outcome measures and assessment procedure

The primary outcome measure is the spatial span task from the Wechsler Memory Scale 3rd edition, assessing spatial working memory at four to six weeks after training (t2/t3) (Table 
1).

**Table 1 T1:** Neuropsychological tests and parental questionnaires at baseline and follow-up assessments

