### Statistical methods

Data will be analysed using the IBM SPSS statistics software for Windows, version 19 (IBM Corp. Released 2010. IBM SPSS Statistics for Windows, Version 19.0. Armonk, NY: IBM Corp, USA) (Illinois, United States). Differences in group means for variables with a normal distribution will be compared with the Student’s *t-*test. Outcome measures not normally distributed will be analyzed using the Mann-Whitney *U* test. The Wilcoxon signed-rank test for two related samples will be used to compare scores at the two time points (baseline versus immediately after training). A univariate general linear model will be used to compute mean values for the neuropsychological tests and questionnaires adjusted for gender and SES, with the group as the fixed factor and sex and the SES as covariates. A full data analysis plan will be drafted before unmasking group adherence.

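### The article contradicts itself on the time of the primary assessment t2 and on when group 2 starts training; one of the four readings would have the control group largely or fully trained at t2

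*Protocol article*

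**What the plan says.** **Time of t2.** Two statements place it at the end of training:

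- Design describes the follow-up visit as "immediately after completed training (after four to six weeks - t2".
- Statistical methods defines the within-child comparison as "baseline versus immediately after training".

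Three statements place it later:

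- Abstract, Methods/Designs: "A neuropsychological assessment will be performed before and 4 to 6 weeks after completed training".
- Design, closing sentence: "The primary endpoint will be the assessment performed at four to six weeks after training (t2 and t3".
- Outcome measures and assessment procedure, for the primary outcome (spatial span): "assessing spatial working memory at four to six weeks after training (t2/t3".

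**Start of group 2.** Design says: "Group 2 will then start training when group 1 has completed its training". The Abstract, having just described the post-training assessment, sets a later condition for the control group: "When the latter assessment has been completed in the intervention group".

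**Length of training.** The Abstract allows 25 sessions over 5 to 6 weeks. The Intervention section gives five days a week for five weeks, which is also 25 sessions.

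**The concern.** Group 2 can serve as an untrained control only while it has not begun the program. Design says that it waits in that role, but the same paragraph starts its training when group 1 finishes and then places the primary assessment four to six weeks after training. Read literally and together, those two statements have group 2 training during the gap, so the comparison at t2 would set a trained group against one well into or through the same program and would be biased towards no difference.

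The readings that keep the control untrained are not interchangeable either. With training of 5 to 6 weeks, t2 falls about 5–6 weeks after the start of training if it is immediate, and about 9–12 weeks after it (5 + 4 to 6 + 6) if it is delayed. The first measures an effect at the end of training, the second an effect that has lasted four to six weeks. The primary outcome section and the Statistical methods section therefore point to different assessments. In a multicentre trial, sites following different sections could run different schedules.

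**Working it through.** No stated sample size or power is in dispute here. The 100 participants cannot be rebuilt from the article, because the mean and SD behind them are not given. The check concerns timing, with a power illustration added.

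**Inputs**

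- Gap from the end of group 1's training to t2: 0 weeks, or 4–6 weeks (sections cited above).
- Length of training: 5 weeks (Intervention) or 5–6 weeks (Abstract), for 25 sessions.
- For the illustration: 80% power, two-sided alpha 0.05 and 100 participants (Estimation of sample size). A split of 50 per arm is my assumption, since no allocation ratio is stated.
- t2 is taken as the between-group comparison, because by Design group 2 has been trained by t3.

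**Step 1: the four combinations**

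| | t2 | Group 2 starts | Group 2's training done at t2 |
|---|---|---|---|
| a | end of training | when group 1 finishes training | 0% |
| b | end of training | after group 1's t2 | 0% |
| c | 4–6 weeks later | after group 1's t2 | 0% |
| d | 4–6 weeks later | when group 1 finishes training | see step 2 |

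**Step 2: share of training done under (d)**

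Share = min(1, gap / length of training); sessions = 25 × share.

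| Gap (weeks) | 5-week training | 6-week training |
|---|---|---|
| 4 | 4/5 = 80%, 20 sessions | 4/6 = 67%, about 17 sessions |
| 5 | 100%, 25 sessions | 5/6 = 83%, about 21 sessions |
| 6 | 100%, 25 sessions | 100%, 25 sessions |

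The range is 80–100% on the 5-week schedule, and 67–100% over all the durations that the article allows.

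**Step 3: illustration of the consequence under (d)**

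The standardised effect implied by the design is d = (1.96 + 0.84) × √(2/50) = 0.56. Assume that benefit is proportional to sessions done. The contrast left at t2 is then 0.56 × (1 − share), with standard error √(2/50) = 0.20. Two-sided power by the normal approximation:

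| Share done by group 2 | Contrast left | Power |
|---|---|---|
| 0% | 0.56 | 80% |
| 67% | 0.19 | about 15% |
| 80% | 0.11 | about 9% |
| 83% | 0.09 | about 7–8% |
| 100% | 0 | 5% (equal to alpha) |

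**Step 4: can the text be read as consistent?**

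The parenthesis in the first t2 statement of Design could mean four to six weeks from the start of training. At week four, however, a child on five sessions a week has done 20 of 25, so training would not be complete. That reading also leaves the conflict with the closing sentence of Design, the Abstract and the primary outcome section.

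**The case against.** The strongest reply is that the Abstract gives a coherent order: train group 1, assess it four to six weeks later, then start group 2. It is the only place that ties group 2's start to the assessment. The sentence in Design can be taken as a looser summary of the same order, since group 1 has indeed finished training by then, and the surrounding sentences make clear that an untrained control is intended. Design also has its own immediate t2, and pairing that with its start rule leaves the control untrained. Figure 1, to which the start rule refers, is not reproduced in the text available here and may show the intended schedule.

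Much of this stands. A reader might infer that the trial plans to compare trained children with trained controls. The documents do not support that: it follows only from combination (d), which sets aside the Abstract's sequence and Design's first t2 statement. A reader might also take 80–100% trained and 5–9% power as the size of the problem. Those figures hold only for the 5-week schedule; the Abstract's 6-week limit widens them to 67–100% and about 5–15%.

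What does not stand is treating the matter as loose wording alone. The two t2 times remain in conflict whichever start rule is used, and they apply to the primary endpoint. A figure might show the intention but cannot make the sentences agree.

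It can also be said that the choice of control data belongs in the analysis plan, which Statistical methods promises before unmasking and which is not shown. Its absence from the article is no fault. The contradictory timing that makes such a rule necessary is stated in the article itself.

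**Conclusion.** The point holds as a contradiction in stated text about the time of the primary assessment and the condition of the control group. It is neither an omission nor a clerical slip. Contamination of the control is a conditional risk, present in one reading of four.

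The shares of training in that reading follow from the article's own durations. The loss of power rests on three further assumptions that the article does not supply: benefit proportional to sessions, equal arms, and an effect back-calculated from the power target. The power figures are an illustration, and the contradiction does not depend on them. In the three other readings the design keeps its nominal power, but the effect being estimated remains undetermined between end of training and four to six weeks later.

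**What to change.** Reconcile the Abstract, Design, Outcome measures and assessment procedure, and Statistical methods so that all give one time for t2 and one condition for the start of group 2. Which schedule applies is for the investigators to settle; this review does not choose it.

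Then state, in the correction or in the promised analysis plan, that the primary comparison uses as control data only group 2 assessments made before that child's first training session, and at the same time since baseline as group 1's t2. Check this against the recorded dates of first session and of t2 for children already enrolled.

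The cost is a clarifying amendment and a check of dates, with no new procedures. Trial status reports recruitment as open until June 2015, so the text can be settled while children are still entering. It should not be left until analysis, because an untrained control assessment cannot be recovered once a child has begun training.
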